### Data collection

An independent project vital registration system has been set up in the 48 study clusters. The system is a modification of one that was successful in the Makwanpur study, the modifications being based on experiences of running less intensive systems in Bangladesh, Jharkhand and Orissa. All births, female deaths, stillbirths, neonatal and infant deaths will be monitored by local resident enumerators. These enumerators will communicate with interviewers, who will confirm each event and visit women and their families in their homes to deliver a postnatal interview at about 6 weeks after delivery. The interview will describe the respondent's demographic background, socioeconomic status and maternity history. Subsequent sections will cover antenatal, delivery, postnatal and neonatal care, as well as responses to illness in mother or infant. In the event of maternal death, stillbirth or neonatal death, supervisory staff will collect verbal autopsy information from family members and triangulate it with information available from health care facility documents.

### Data management

Hard copy questionnaires are transferred to the central office weekly. Two types of data are entered into electronic relational database management systems in Microsoft Access. Births and deaths are entered into a database dedicated to tracking follow-up and generating mortality rate outcomes. Interview questionnaires are entered into a separate database. Both databases include validation constraints and enforce referential integrity. All information provided by participants remains confidential. Access is restricted to interviewers, supervisors, data auditors, and officers, and research staff at the analytical level. No analyses or outputs include the names of participants.

### Quality control

The trial is headed by a project coordinator. Data collection activities are managed by 2 project officers, each responsible for 3 urban wards. 99 female residents of the project clusters are tasked with identifying births and deaths in their areas. Each event is crosschecked by a female cluster interviewer responsible for 4 clusters, who visits the home to verify it and to discuss a follow-up visit with family members. This process is quality controlled by a further visit by a female supervisor responsible for 8 clusters (1 ward) to confirm every fifth event. When interviews are completed, each is checked by the interviewer in the field and by a supervisor. Supervisors also visit homes to crosscheck the data from every 10^th ^interview and to ensure valid responses to queries arising from crosschecking, and make random visits to observe interviews. Every third interview tool is crosschecked by a project officer. Supervisors and officers meet weekly to review progress and issues arising. All questionnaires and memoranda are crosschecked at the central office. Data entry includes internal validation rules. Entered data are internally crosschecked by the data management officer for every 10^th ^questionnaire, and externally crosschecked against every 15^th ^questionnaire.

### Dealing with loss-to-follow-up

Although all trials have to deal with loss-to-follow-up, slum communities in Mumbai have some special features. Our estimates suggest that some areas experience 25% annual in- and out-migration. Further, many residents retain connections with their family homes in other parts of India. A number of specific problems arise for birth outcome tracking: (a) residents of other places may come to the city for delivery; (b) residents of slum areas may go to their family homes for delivery (within or outside Mumbai), or for a variable period shortly after it; and (c) instability of tenure and livelihood may contribute to mobility within and outside slum areas; (d) working women may not be available for interview; (e) demolition of parts of or whole slum areas as part of urban infrastructure initiatives. We are attempting to deal with these issues in the trial, by three main methods. First, we have designed the household surveillance in order to achieve 100 annual births per cluster after potential loss-to-follow-up of 25%. Second, interview times will be flexible and multiple visits have been planned for. Third, the parallel database systems optimise the available information: for a large number of deliveries, we are able to ascertain the outcome at one month postpartum, even if the interviewers do not succeed in completing an interview. This allows us to generate mortality rates from a larger tranche of data, while using interview data from a smaller tranche for the secondary outcomes.

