#### Ancillary questions

What are the patterns of maternal and neonatal care in vulnerable slum communities in Mumbai?

What are the neonatal mortality rates in vulnerable slum communities?

How can we assess health vulnerability, how does a cluster-level classification compare with an individual-level one, and is this classification associated with health outcomes?

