### Sample size

We aim to accumulate data on 300 births per cluster over 3 years, which implies a cluster size of 900–1400 households on the basis of municipal demographic data. The surveillance of births and birth outcomes will be carried out in 48 clusters of 1000–1500 households. Sample size was predicated on the primary outcome of neonatal mortality rate. Calculations were based on the equations of Hayes and Bennett,[41] assuming two treatment groups, unmatched clusters of approximately equal size, a value of *k *– the between-cluster coefficient of variation – equal in intervention and control groups, and the addition of 2 to the estimated cluster number to account for loss of degrees of freedom consequent on stratification. The value of *k *was set at 0.3 on the basis of (a) available estimates of infant mortality rate in 24 wards of Mumbai from 2003 municipal data, and (b) estimates of neonatal mortality rate from the Makwanpur study in Nepal. Sample size was estimated for a range of births per cluster (200–350) and a range of possible reductions in neonatal mortality rate. At 80% power and two-tailed 5% significance level, the sample size will allow us to detect a reduction in neonatal mortality rate from 30 to 20 per thousand live births. We are aware of a secular trend to decreasing mortality in urban India, and have provisionally analysed vital events for the inception year of the project. If neonatal mortality rates are lower than suggested by the available figures, the sample size will allow us to detect a fall from 20 to 12 per thousand live births at 80% power. Both estimates project significance for a fall of roughly a third in neonatal mortality rate.

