### Economic evaluation

We will conduct an economic evaluation along the lines of the cost-effectiveness work that we have previously published.[43] Trial expenditure is entered into accountancy software (Tally 7.2, Tally Solutions Pvt Ltd, India) under cost codes. We shall evaluate cost-effectiveness in terms of life years saved (LYS), with appropriate discounting.

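### Mortality rates appear to rest on deliveries with a known one-month outcome, which can bias the rate, probably upward, and the comparison too if tracing differs by arm

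*Protocol article*

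**What the plan says.** The section Dealing with loss-to-follow-up lists reasons why birth outcomes are hard to track. One is that "residents of slum areas may go to their family homes for delivery", or may be away for a time soon after it. The section names three remedies: surveillance sized for 25% loss, flexible and repeated interview visits, and two parallel databases. On the third, it says that for many deliveries, though not all, "we are able to ascertain the outcome at one month postpartum" even where no interview is completed. It continues: "This allows us to generate mortality rates from a larger tranche of data", with the smaller interviewed set used for secondary outcomes.

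Analysis strategies compares stillbirth and neonatal mortality between arms with hierarchical logistic models. Its intention-to-treat rule keeps people who move to another cluster in their original one. It does not mention infants whose one-month status is unknown.

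Neonatal mortality is the outcome on which the trial was sized: "Sample size was predicated on the primary outcome of neonatal mortality rate". Its absolute level is also used elsewhere:
- Ancillary questions asks "What are the neonatal mortality rates in vulnerable slum communities".
- Interim analyses and stopping rules uses the baseline rate to review cluster size.
- Economic evaluation measures cost-effectiveness in life years saved.

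**The concern.** Deaths and survivors become known in different ways. An infant who dies on day 2 has a final outcome on day 2. A survivor has one only if someone can establish at one month that the child is alive. If the family leaves in between and is not traced, a potential survivor is lost from the data, whereas an earlier death is not. A rate computed among known outcomes is then too high.

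The three remedies do not remove this selection. More births per cluster restores numbers. Repeated visits and parallel databases raise the share that is traced, but the protocol itself says that share is not complete.

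Two things are at stake. The first is the absolute rate and the absolute difference, which feed the ancillary question, the cluster-size review and life years saved. The second is the comparison between arms. It is safe only if tracing is similar in both, and allocation is open while the intervention aims to change delivery, postnatal and newborn care.

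**Working it through.** **The plan's own figure.** Sample size states "At 80% power and two-tailed 5% significance level" that the trial can "detect a reduction in neonatal mortality rate from 30 to 20 per thousand live births". Inputs from that section are m = 300 births per cluster, k = 0.3 and 2 added clusters. The Hayes–Bennett formula for unmatched proportions is

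c = 2 + (1.96 + 0.84)² × [p0(1−p0)/m + p1(1−p1)/m + k²(p0² + p1²)] / (p0 − p1)²

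- For 30 against 20: (0.0291 + 0.0196)/300 = 0.0001623, and 0.09 × (0.0009 + 0.0004) = 0.000117. The sum divided by 0.0001 is 2.793. Multiplied by 7.849 this is 21.92, and adding 2 gives 23.92, so 24 per arm. The plan's figure is reproduced.
- For 20 against 12 the same formula gives 20.86, so 21 per arm, within the 24 available.

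The calculation assumes that the observed rates equal the true ones.

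**Bias formula.** Let p be the true rate, Ls the share of survivors with unknown one-month status, and Ld the share of deaths that are missed. Among known outcomes,

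observed = p(1−Ld) / [p(1−Ld) + (1−p)(1−Ls)]

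Ls and Ld are assumptions. The protocol gives only an overall 25% loss allowance and 25% annual migration in some areas. Spread evenly, that migration is 0.25 × 28/365, or about 2% over 28 days, excluding temporary travel around delivery. So 2% serves as a low illustration and 25% as an upper one.

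**Level, with no deaths lost (Ld = 0), per thousand:**

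| Ls | true 30 | true 20 |
|---|---|---|
| 2% | 30.6 | 20.4 |
| 5% | 31.5 | 21.0 |
| 10% | 33.2 | 22.2 |
| 15% | 35.1 | 23.5 |
| 25% | 39.6 | 26.5 |

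Worked case: 30 / (30 + 970 × 0.75) = 30/757.5 = 39.6 per thousand. At 25% the true difference of 10 per thousand reads as 39.6 − 26.5 = 13.1.

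**Direction when deaths are also lost (true 30, Ls = 25%):**
- Ld = 12.5% gives 34.8.
- Ld = 25% gives 30.0, so no bias.
- Ld = 37.5% gives 25.1, so the bias reverses.

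**Ratio, equal loss.** With Ls = 25% in both arms and Ld = 0, the ratio for 30 against 20 is 0.669; the true value is 0.667.

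**Ratio, unequal loss, no true effect, rate 30, Ld = 0:**
- Control 25%, intervention 20%: 37.2/39.6 = 0.94. With the arms reversed it is 1.06.
- Control 25%, intervention 15%: 35.1/39.6 = 0.89.
- Control 10%, intervention 5%: 31.5/33.2 = 0.95.

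On the log scale, 0.94 is about 15% of the planned effect (ln 0.94 / ln 0.667) and 0.89 about 30%.

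**The case against.** The strongest reply is that the protocol never says infants with unknown status leave the denominator. The sentence contrasts deliveries with and without a completed interview and describes a measure that improves ascertainment; missing-outcome rules may sit in an analysis plan that is not shown. It is true that the exclusion is inferred. But the text does tie the mortality data set to ascertained outcomes, and a logistic model needs a known 0 or 1. Counting unknowns as alive would not solve the problem either, since it misses deaths after departure and errs the other way.

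Second, leaving is not the same as being lost. Absence may be temporary, enumerators are local residents, each event is verified at home, and the interview falls at about six weeks, after the neonatal period. This stands, and it is why 25% is an upper illustration. That figure is an allowance for total loss, in a section whose list of problems includes women unavailable for interview. It is not the share of infants with unknown vital status.

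Third, a reader might infer that the rate is certainly inflated. The documents do not support that. Births away may never be registered, deaths after departure may be missed, and families may leave after a death. Any of these can offset or reverse the bias.

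Fourth, a reader might infer that the primary comparison is biased. Nothing in the protocol shows that women's groups change travel after delivery, and evaluation and intervention teams work independently. A difference in tracing is possible, not shown.

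**Conclusion.** The concern holds as a conditional one. On its natural reading, the plan analyses known one-month outcomes in a setting where departures soon after birth are expected, and neither the named remedies nor the intention-to-treat rule removes the resulting selection. The likely direction is upward, but the documents do not fix it. If no deaths are missed and 2–25% of survivors are unknown, the rate is overstated by about 2–32%. If deaths and survivors are lost equally there is no bias. The rate ratio is safe under equal loss; a gap of 5 to 10 percentage points between arms would move it by about 5–11%. Every loss rate here is an assumption. The point deserves a change to the plan because the remedy is cheap, not because an error in the result has been shown.

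**What to change.** 1. Define the denominator as every verified live birth to cluster residents, whether or not an interview is completed or a one-month outcome obtained.
2. Record the infant's vital status, with its date, at the home verification visit described under Quality control. The protocol does not say this is done, so it must be confirmed or added.
3. Analyse death to 28 days with infants censored at the last date known alive. One option is a discrete-time hierarchical logistic model with early and late neonatal intervals. Make it the main analysis, or at least a prespecified sensitivity analysis beside the binary model.
4. Report the number and share with unknown one-month status by arm.

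The cost is modest: a dated item at a visit that already takes place, and a slightly more complex model. The design and cluster numbers do not change. Censoring assumes that departure is unrelated to the later risk of death, and the fix does nothing for births or deaths away from the cluster that are never registered.

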### Interim analyses and stopping rules

There will be two types of interim analysis. (1) An *analysis of baseline findings*, particularly neonatal mortality and care-seeking practices. The analysis will not look at outcomes in terms of allocation. The results will provide us with estimates of neonatal mortality rates on the basis of which cluster size will be reviewed. (2) An *interim analysis of outcomes*. This will be conducted in late 2008. The analysis will look at the outcomes in terms of allocation. At this point a Data Safety Monitoring Board (DMB) will be convened according to the DAMOCLES statement.[42] The DMB will examine the study for deviations from protocol and preliminary results. It is unlikely that a community mobilisation intervention will have adverse effects. From our experience in other, similar studies, we do not intend to institute stopping rules. However, if there are social or political problems in specific clusters, each situation will be judged on its merits and the trial can be stopped if necessary. The DMB will also advise on whether the trial should be extended to achieve greater power.

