### Analysis strategies

The analysis will be undertaken as intention-to-treat at both cluster and participant levels. Participants who begin the trial as residents of a given cluster will be retained as residents even if they move to another cluster during the trial period. Within the prospective cohort, stillbirth and neonatal mortality rates will be compared in control and intervention groups, taking account of clustering, with hierarchical logistic models. Intraclass correlation coefficients will be estimated from preliminary surveillance of neonatal mortality and stillbirth data by analysis of variance. Secondary outcomes and process indicators will also be compared with adjustment for clustering. All estimates will be presented with 95% confidence intervals.

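### Baseline cluster values of care seeking are available in all 48 clusters, but the stated comparisons of care and uptake outcomes do not use them as a covariate

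*Protocol article*

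**What the plan says.** The Design section of the protocol article states that outcome surveillance is in place in all 48 clusters. Under Sample size the investigators report that they "have provisionally analysed vital events for the inception year of the project". Under Interim analyses and stopping rules, a baseline analysis not split by allocation will look at findings, "particularly neonatal mortality and care-seeking practices", and the mortality estimates will feed a review of cluster size. Under Analysis strategies, preliminary surveillance also supplies the intraclass correlations for neonatal mortality and stillbirth.

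For the comparison itself, Analysis strategies names hierarchical logistic models that allow for clustering for stillbirth and neonatal mortality. For the rest it says: "Secondary outcomes and process indicators will also be compared with adjustment for clustering". No baseline term is mentioned.

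On the count of births, Sample size says "We aim to accumulate data on 300 births per cluster over 3 years", and the loss-to-follow-up section says that surveillance is sized to "achieve 100 annual births per cluster after potential loss-to-follow-up of 25" per cent. Neither statement is tied to the date on which group meetings begin.

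**The concern.** Care practices and service uptake make up two of the three outcome tiers. In a cluster trial, the precision of such outcomes is governed mainly by variation between clusters, and with 24 clusters per arm that variation is averaged over few units. A pre-intervention measurement of the same outcome in the same cluster is usually the best available predictor of it. The trial has this measurement but states only design uses for it. At stake is avoidable width in the confidence intervals for these outcomes, and less protection against chance baseline differences between arms.

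A second, smaller matter is that a covariate counts as baseline only if the births behind it precede the intervention. The protocol gives no date that separates baseline births from outcome births.

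**Working it through.** **Inputs from the protocol.** 24 clusters per arm; 300 births per cluster over three years, 100 per year; between-cluster coefficient of variation k = 0.3; two clusters added for lost degrees of freedom (taken as per arm); two-sided 5%, 80% power; neonatal mortality 30 to 20 per 1000, with a fallback of 20 to 12.

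**Assumptions, not in the protocol.** About 100 baseline births per cluster (one year at the planned rate); correlation over time of true cluster values, ρ, of 0.5, 0.8 or 1; intraclass correlation (ICC) for care outcomes of 0.02 to 0.10.

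**1. The plan's own figure.** The Sample size section claims 80% power for a change in "neonatal mortality rate from 30 to 20 per thousand live births". By the Hayes-Bennett formula for proportions,

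c = 2 + (1.96 + 0.84)² × [(p0(1−p0) + p1(1−p1))/m + k²(p0² + p1²)] / (p0−p1)².

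With m = 300, the bracket is 0.0487/300 + 0.09 × 0.0013 = 0.000279. Then c = 2 + 7.85 × 2.793 = 23.92, so 24 per arm. Power at 24 is 80.1%. The stated figure reproduces. The fallback, "detect a fall from 20 to 12 per thousand live births at 80% power", needs 20.9 clusters per arm and has 85.7% power at 24, so the stated 80% is conservative.

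**2. Care and uptake outcomes.** Adding the baseline multiplies the variance by 1 − ρ² × R_base × R_follow, where R = m × ICC / (1 + (m−1) × ICC). With 100 baseline and 300 outcome births:

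| ICC | R_base | R_follow | Variance factor, ρ = 0.5 | SE cut | Variance factor, ρ = 0.8 | SE cut |
|---|---|---|---|---|---|---|
| 0.02 | 0.671 | 0.860 | 0.856 | 7.5% | 0.631 | 20.6% |
| 0.05 | 0.840 | 0.940 | 0.802 | 10.4% | 0.494 | 29.7% |
| 0.10 | 0.917 | 0.971 | 0.777 | 11.9% | 0.430 | 34.4% |

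With 200 outcome births instead of 300, the cuts are 7.0-11.7% at ρ = 0.5 and 19.1-33.8% at ρ = 0.8. Over both cases the ranges are therefore about 7-12% and 19-34%. Charging one between-cluster degree of freedom (22 to 21.5 effective clusters per arm) raises the standard error by √(22/21.5) − 1 = 1.2%, so the lowest cut of 7.0% becomes about 6%.

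**3. Neonatal mortality.** At 30 per 1000, 100 births give about 3 baseline deaths per cluster. Baseline reliability is (0.3 × 0.03)² / [(0.3 × 0.03)² + 0.03 × 0.97/100] = 0.000081/0.000372 = 0.218. It is 0.155 at 20 per 1000.

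| ρ | Variance factor | Power, 30 to 20 | After the degree-of-freedom charge |
|---|---|---|---|
| none (no adjustment) | 1 | 80.1% | – |
| 0.5 | 0.977 | 81.0% | 80.1% |
| 0.8 | 0.942 | 82.4% | 81.6% |
| 1 | 0.909 | 83.7% | 82.9% |

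The chance that a cluster has no baseline death is 0.97^100 = 4.8% at 30 per 1000 and 0.98^100 = 13.3% at 20 per 1000. That is roughly 2 to 6 of the 48 clusters, and their baseline log-odds would be undefined.

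**4. Birth window, conditional scenarios only.** For 30 to 20 per 1000 at 24 clusters per arm:

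- 300 births per cluster, all after the start: 80.1%.
- One of the three years is pre-intervention and is counted: the intervention-arm rate becomes 30 − (2/3) × 10 = 23.3 per 1000, and power is 43.5%. With half a year counted, it is 63.0%.
- That year is excluded and not replaced (200 births per cluster): 69.5%.

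**The case against.** The strongest reply is that this is a journal article. The covariate set and the exact analysis window commonly sit in the full protocol or analysis plan, and allowance for clustering does not exclude further adjustment. That stands as a reason not to call the omission an error. The point is an improvement on the method as stated.

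The size of the gain can also be challenged. No cluster-level figure for care practices and no correlation over time is given. The loss-to-follow-up section reports 25% annual in- and out-migration in some areas, as well as demolition, and both weaken persistence. Ward stratification may already absorb part of the variation. All of this stands, and it is why the result is a range with a plausible lower end.

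Four stronger readings are tempting, and the protocol supports none of them:

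- **Early data go to waste.** They serve the cluster-size review and the intraclass correlations.
- **The unadjusted comparison is biased.** Clusters were randomised four against four within each ward, and chance imbalance is reflected in the cluster-adjusted interval. The loss is one of efficiency.
- **The primary outcome loses much precision.** The mortality gain is between nothing and about three power points after the degree-of-freedom charge.
- **Pre-intervention births dilute the effect.** No section says that inception-year births count towards the 300. The interim-analysis section separates baseline findings from outcomes, and the comparison is placed within a prospective cohort.

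**Conclusion.** The point holds for care-practice and uptake outcomes. The baseline values exist in every cluster, the stated comparisons do not use them, and including them would narrow standard errors by about 7-12% at a correlation over time of 0.5, or 19-34% at 0.8. This rests on an assumed intraclass correlation of 0.02 to 0.10 and about 100 baseline births per cluster. For neonatal mortality, adjustment is optional, since power moves from 80.1% to about 80-83%.

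The undated birth window calls for a clarification and is not a defect in its own right. A reader might infer that the trial has only about 44% power. That figure applies only if a full pre-intervention year were counted among the three, which the protocol nowhere says.

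**What to change.** Add to Analysis strategies that each comparison of a care-practice or uptake outcome includes the cluster's baseline proportion of that same outcome as a cluster-level covariate. If neonatal mortality is adjusted in the same way, use the baseline proportion and not the log-odds, because some clusters will have no baseline deaths. Settle this before the late-2008 analysis by allocation.

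As a clarification, state that the 300 births per cluster and the outcome comparison use births from a fixed calendar date, identical in both arms and not before group meetings start, and that earlier births serve as baseline.

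The covariate needs no new data and costs one between-cluster degree of freedom per model. The date costs only wording if the three years already begin after the start of meetings. If they include the inception year, 200 births per cluster remain and power is 69.5%, unless surveillance runs long enough to replace them.
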